##### Secondary outcome measures

The following secondary outcome measures will be assessed to detect differences among both feeding protocols:
Evolution of values (i.e. the trend of the assessed parameters during the 7-day study period) for anabolic and catabolic pathways (ubiquitin-proteasome and autophagy) which control muscle metabolism as identified by proteomic analysis of vastus lateralis muscle biopsies prior to the start of nutrition and on day 7 in both study groupsQuadriceps muscle area and diameter by ultrasound prior to start of nutrition and on day 7 in both study groupsAmount of gastric residual volume (GRV) in millilitres per day and assessed after every nutrition cycleNumber of events of diarrhoea, constipation, meteorism, nausea, regurgitation, vomiting and pulmonary aspiration per feeding cycle:
Acute diarrhoea over ≥ 3 unformed to liquid bowel movements within 24 h and with a total weight of > 250 g per day are present.Constipation is diagnosed if the defecation is more difficult and takes place less than three times a week; in the study, constipation will be defined at ≥ 3 days without bowel movements, whereby investigators must influence the stool regulation with medication.Amount of regurgitation in millilitres per day and assessed after every nutrition cycle.Assessment of glucose values (mmol/l) for assessment of effect on glucose metabolismAssessment of urea (mmol/l) once daily as a marker for amino acid degradationAssessment of IGF-1 (insulin-like growth factor 1) once daily due to its influence on the MPS pathwayAssessment of Acute Physiology and Chronic Health Evaluation (APACHE II; for severity of disease) and Simplified Acute Physiology Score (SAPS II; for risk of mortality) upon study inclusion (baseline), and daily assessment of Sepsis-related Organ Failure Assessment (SOFA; for degree of organ dysfunction)Nutrition Risk in Critically Ill (NUTRIC) score including interleukin-6 upon study inclusion (baseline)

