#### Sample size

Power analysis and sample size estimation were performed a priori using G*Power 3.1. We assumed a final 2-way repeated measures analysis of variance (ANOVA) and set a sample size to ensure at least 90% power (1 − *β* = 0.9) at a significance level of 1% (*α* = 0.01).

The effect size was estimated according to our feeding previous protocols (Tables 1 and 2): the average administered protein was 1.6 g protein/kg BW/24 h at 34 h in the experimental group and 1.3 g protein/kg BW/24 h at 36 h in the control group. The estimation of the mentioned daily protein targets in this study was based on a preceding prospective observational pilot feasibility study with a high-protein formula (manuscript currently under review). For practical reasons, the 2-h difference was deemed negligible. Protein targets have been chosen in accordance with the current guidelines for enteral nutrition [35–41]. For the time series analysis, a moderate correlation between consecutive time points (0.5, Hinkle et al. [42]) was assumed. The 20 time points were chosen according to the four scheduled measurements and calculation of applied amount of protein across each study day for a specified minimum follow-up of 5 days (see inclusion criteria).

Sixty patients are required to have a 90% chance of detecting an increase from 1.3 g protein/kg BW/24 h in the control group to 1.6 g protein/kg BW/24 h in the experimental group after 36 h.

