#### Plans to promote participant retention and complete follow-up

The defined eligibility criteria lead to participant retention due to inclusion of patients expected to stay at least 5 days in ICU.

In case of study withdrawal or early discharge within days 1–4 of the study, all data will be destroyed, and the patient will be replaced. Except for patients with early discharge to the general ward (e.g. before study day 5), the study team will attempt to continue the study: all study procedures will be continued including allocated feeding protocol, study laboratory and the ultrasound and muscle biopsy on day 7 of the study. If there is no possibility to continue enteral feeding on general ward, the patient will be replaced.

If the patient is discharged on day 5 or 6 of the study, we will perform the ultrasound and muscle biopsy on the day of discharge and accept missing data of the residual day(s).

If the patient is withdrawn from the study within days 5–7 of the study, the patient or his next of kin will be asked for use of the data already recorded. If applicable, we will also ask for use of regular data registered thereafter in the ICU setting.

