##### Primary and secondary analysis

A 2-way repeated measures ANOVA with post hoc pairwise comparison using a Bonferroni correction will be used to test for differences in protein administration at each time point for the control and experimental groups. The same method will be used to test differences in all secondary outcomes between groups. Additional statistical modelling using generalised linear models will be performed to inspect relationships between baseline patient characteristics, and primary and secondary outcomes.

All analyses on primary and secondary endpoints will be calculated by the study team in close collaboration with the Clinical Trial Unit of the University Hospital Basel.

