#### Methods in analysis to handle protocol non-adherence and any statistical methods to handle missing data

Despite the low number of participants, no considerable amount of missing data is expected due to the close observation of patients on the ICU in addition to our stipulations for replacing withdrawn patients according to the protocol. As described under the “Patient informed consent” section, the patients and their next of kin will have the option to agree to study participation whilst rejecting performance of muscle biopsies. Nevertheless, the study team is interested in obtaining as much study data as possible but will accept missing data on secondary outcomes due to lack of consent for the muscle biopsy. Patients with missing muscle biopsies will not be replaced. No imputation of missing data will be performed for statistical analysis.

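### Daily and per-cycle secondary outcomes end at a day-5 or day-6 discharge, but the fixed repeated-measures ANOVA without imputation cannot use incomplete seven-day series

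*Protocol article*

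**What the plan says.** *Study period* sets seven days from the start of feeding. *Days 1–7 of observation*, *Glucose, urea and IGF-1 evolution over study period* and *Assessment of study scores* provide for daily laboratory values and SOFA. *Secondary outcome measures* has gastric residual volume (GRV) assessed after every feeding cycle.

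*Participant timeline* lets closeout fall on the day of ICU discharge if that comes first. For discharge on day 5 or 6, *Plans to promote participant retention and complete follow-up* moves ultrasound and biopsy to the discharge day and will otherwise "accept missing data of the residual day(s"). The same section tries to continue study procedures on the ward after discharge before day 5. It states no such effort for days 5 and 6.

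*Primary and secondary analysis* names a 2-way repeated-measures ANOVA for protein administration and adds: "The same method will be used to test differences in all secondary outcomes between groups". The section on non-adherence and missing data states: "No imputation of missing data will be performed for statistical analysis". That section expects little missing data, citing close ICU observation and replacement of withdrawn patients. The only accepted gap it names is refused biopsies.

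**The concern.** The three rules do not fit together. Collection stops by design for an identifiable group, the named test needs complete series, and the usual means of completing a series is excluded.

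Taken literally, the plan leaves two routes. Either a patient without day 6 or 7 is removed together with the days that were observed, or the late time points compare only patients still on study. Those who leave early have probably recovered faster, so both routes shift the sample towards slower recoverers. If one regimen speeds recovery, it could lose more of its better patients. Late changes in urea, IGF-1 or SOFA could then reflect who remains rather than how they were fed.

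**Working it through.** **1. The plan's own figures.** The protocol gives no day-5 or day-6 discharge rate and no power statement for secondary outcomes. Its one calculation (*Sample size*) concerns the primary protein series: N = 60, alpha 0.01, "to ensure at least 90% power", correlation 0.5, and 20 time points (4 per day × 5 days). No SD or Cohen's f is stated, so 60 cannot be reproduced forwards. Solved backwards for the between-groups test, λ = f²·N·m / (1 + (m − 1)ρ), it implies f = 0.3715:

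λ = 0.1380 × 60 × 20 / (1 + 19 × 0.5) = 165.6 / 10.5 = 15.8, which gives power 0.90 on F(1, 58).

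This serves below only as a yardstick.

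**2. What is missing and what would be discarded.** Assume the discharge-day value is taken.

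| Discharge | Daily values seen (of 7) | GRV cycles seen (of 4 × 7 = 28) |
|---|---|---|
| Day 5 | at most 5 | at most 20 |
| Day 6 | at most 6 | at most 24 |

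If 6 of 60 patients (10%, assumed) left on day 5, 6 × 2 = 12 daily values per outcome would be missing. Removing these patients would discard a further 6 × 5 = 30 observed values. If they left on day 6, 6 would be missing and 36 discarded.

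**3. Whether this is foreseeable.** Eligibility needs an expected ICU stay of only 5 days. Feeding starts at the earliest on the morning after inclusion. A patient included on ICU calendar day 1 therefore has study day 1 on ICU day 2 and study day 7 on ICU day 8. A stay ending on ICU day 6 or 7 is a study-day 5 or 6 discharge. The protocol's own rules for such discharges show that they were expected.

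**4. Precision.** If a share q is removed equally from both arms, the standard error grows by 1/√(1 − q). The last column shows a hypothetical outcome with 90% power at N = 60 and alpha 0.01, with λ scaled by N/60.

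| q (assumed) | N left | SE factor | λ | Power of the hypothetical outcome |
|---|---|---|---|---|
| 0% | 60 | 1.00 | 15.8 | 0.90 |
| 10% | 54 | 1.05 | 14.2 | 0.86 |
| 20% | 48 | 1.12 | 12.6 | 0.80 |
| 30% | 42 | 1.20 | 11.0 | 0.73 |
| 40% | 36 | 1.29 | 9.5 | 0.64 |

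**5. Bias.** This was examined by an illustrative simulation: seven daily values, correlation 0.5, 2000 runs per scenario, discharge depending on the patient's own recovery, and a true difference of about 0.78 SD. All of these are assumptions.

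| Discharge rule | Patients removed | Full data | Complete cases | Shrinkage |
|---|---|---|---|---|
| Same in both arms | 13% | 0.775 | 0.696 | 10% |
| Same in both arms | 32% | 0.788 | 0.660 | 16% |
| Same in both arms | 50% | 0.785 | 0.636 | 19% |
| One arm more readily | 21% | 0.773 | 0.596 | 23% |
| One arm more readily | 42% | 0.780 | 0.517 | 34% |
| One arm more readily | 58% | 0.773 | 0.487 | 37% |

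Shrinkage is 1 − complete cases / full data, for example 1 − 0.696/0.775 = 10%. With no true effect and the same rule in both arms there was no bias. With arm-dependent discharge, a spurious difference of 0.06 to 0.12 SD appeared. A harsher set-up, in which a SOFA-like score itself triggers discharge, took a true difference of −0.90 to −0.45 with 28% discharged. The size is therefore driven by assumptions.

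**6. What is not affected.** The target is hypothesised to be reached within 36 h. Day 5 starts 4 × 24 = 96 h after the first feed, so time to target is normally known long before. A day-6 discharge leaves all 20 points of the sized protein series intact; a day-5 discharge can lose only that day's last cycles. Ultrasound and biopsy are done at discharge, so they are earlier but not missing.

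**The case against.** The strongest reply is that listwise deletion is nowhere stated. Detailed methodology is left to a statistical analysis plan that is not shown, and that plan might fit incomplete series differently. This stands as a limit on certainty. It does not remove the point, because the protocol itself fixes both the ANOVA and the absence of imputation, and the two together leave no sound place for an incomplete series.

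Several stronger readings are tempting but unsupported:

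- **The trial's 90% power falls to 64–86%.** The power statement belongs to the five-day protein series. None is made for the outcomes discussed here.
- **The group comparison is biased.** Bias requires outcome-related discharge together with a treatment effect or arm-dependent discharge. The documents establish neither.
- **The protocol's phrase "the trend of the assessed parameters during the 7-day study period" sets a seven-day trend for the laboratory values.** It sits on the biopsy item. The daily seven-day schedule comes from the other sections cited above.
- **The expectation of little missing data contradicts the discharge rule.** Without a discharge rate, nobody can say that the loss is considerable. The fair criticism is omission: neither reason given covers patients who have left the ICU and are not replaced.
- **Days 1–5 are complete for everyone.** A day-5 discharge can miss part of day 5.

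**Conclusion.** The point holds for GRV, glucose, urea, IGF-1 and SOFA. As written, the plan either discards patients discharged on day 5 or 6 or changes the compared sample on days 6 and 7. Some loss of precision is certain if any such patient is removed: a 5% to 29% wider standard error for 10% to 40% removed. Bias is a risk rather than a finding; under the main simulation's assumptions, estimates shrank by 10% to 37%. The true size is unknown because the documents give neither the discharge rate nor the variances. The primary conclusion is not threatened. This should be corrected, but it is not fatal.

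**What to change.** In *Primary and secondary analysis*, replace repeated-measures ANOVA for these outcomes by a linear mixed model for repeated measures. Include group, time, group by time, and the baseline value where one is collected, and fit the model to all observed data of every analysed patient, including those discharged on day 5 or 6. This is not imputation, so the ban on imputation can stay. An unstructured covariance is feasible for seven daily values (7 × 8 / 2 = 28 parameters). For 28 GRV cycles it would need 28 × 29 / 2 = 406 parameters, so a structured form should be named there.

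Add a supporting comparison over days 1–4, or up to the last time point observed for all analysed patients. In the missing-data section, acknowledge the residual days that the discharge rule accepts as missing, and report their number by arm. Describe death and withdrawal on days 5–7 separately, since they are not recovery.

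The cost is wording and a different model call, with no new data. The downside is that the model assumes data are missing at random given the observed days.

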#### Data management

Study data will be collected and managed using REDCap electronic data capture tools hosted at University Hospital Basel [50]. REDCap is a secure, web-based application designed to support data capture for research studies. REDCap provides (1) an intuitive interface for validated data entry, (2) audit trails for tracking data manipulation and export procedures, (3) automated export procedures for seamless data downloads to common statistical packages and (4) procedures for importing data from external sources.

All data, including demographic data, visit dates, randomisation number and serious adverse events (SAEs), related to this study will be kept within the trial master file (TMF) and the REDCap eCRF. A unique patient study code will be assigned to every screened patient consisting of the prefix PBN (Pro BoNo) plus consecutive numbering for every included patient (e.g. PBN-1). This code will be used to identify all study-specific data (e.g. ultrasound images, blood parameters). The trial will be terminated after collecting data from 30 patients in each group. The signed informed consent forms will be kept in the investigator site file (ISF). To minimise bias, we will set range checks for data values within the eCRF. Data will be archived dually on an external hard disk and on our in-house server system with a backup every 24 h. The hard disk and all physical study data will be stored in a designated place on our ICU at the University Hospital Basel for a minimum of 10 years after study termination or in case of premature termination of this study.

SAEs will be documented in the REDCap eCRF and on paper documents.

Only the study team will have access to study-related data. In case of a patient’s ex post denial of study participation, the data collected will not be used for publication in the present trial or in future trials. In such cases, the data will be destroyed.

#### Confidentiality

Except for the identification log and the informed consent, no study documentation will disclose the patient’s name. No personal identifying data will be registered within REDCap. Backtracking of personal data will only be possible using the identification log securely stored in the ISF. Access to the ISF will only be authorised to the study team and to staff performing monitoring visits.

#### Plans for collection, laboratory evaluation and storage of biological specimens for genetic or molecular analysis in this trial/future use

Proteomic analysis of muscle biopsies will be done prior to start of feeding and on day 7 in both study groups.

Study team members will be permitted to perform muscle biopsies after training with the head of the Neuromuscular Center of the University Hospital Basel. Biopsies of the vastus lateralis of the quadriceps muscle will be performed under local anaesthesia. A 14G disposable spring-loaded fine needle (Bard® Max-Core® Disposable Core Biopsy Instrument, Bard Biopsy, Arizona, USA) will be used. The biopsy will be taken at a penetration depth of 22 mm and maximal sample notch of 19 mm. The biopsies will be snap-frozen and stored at − 80 °C and processed histologically by the Department of Biomedicine of the University Hospital Basel. To evaluate the effect of IF and CF on muscle protein synthesis, proteolysis via the ubiquitin-proteasome pathway, autophagy flux and activation of signalling pathways will be determined. Protein kinase B [1, 3, 8, 25, 51–53], insulin-like growth factor 1 receptor [3, 54], glycogen synthase kinase 3-beta [3, 8, 52], mammalian target of rapamycin (mTOR) [1, 3, 8, 25, 51–54], eukaryotic initiation factors 2 [8, 25] and 4 [1, 8, 25, 51–54] and 70-kDa ribosomal protein S6 kinase [1, 3, 8, 25, 51–54] of the muscle biopsies will be quantified, and their activation level (mainly phosphorylation) will be determined. For the catabolic pathway, forkhead box class O-3 [1, 3, 52, 54], muscle atrophy F-box [1, 3], muscle ring-finger protein-1 [1, 3, 52] and nuclear factor kappa-beta [1, 3] will be measured. For information about autophagy, ULK1 [54, 55], light-chain 3 [55, 56] and p62 [55, 56] will be analysed. For an overview of enzyme regulation, AMP-activated protein kinase [8, 25, 53–55] will be studied.

### Statistical methods

#### Statistical methods for primary and secondary outcomes

Detailed methodology for summaries and statistical analyses of the data collected in this study will be documented in a statistical analysis plan elaborated with the Clinical Trial Unit of the University Hospital Basel.

##### Hypothesis

We hypothesise that target quantity of protein of at least 1.5 g protein/kg BW/24 h is reached earlier (i.e. within 36 h) in patients with IF than in those with standard CF.

##### Datasets to be analysed, analysis populations

An intention-to-treat and per protocol analysis of ICU patients who meet all inclusion and no exclusion criteria will be performed.

##### Primary and secondary analysis

A 2-way repeated measures ANOVA with post hoc pairwise comparison using a Bonferroni correction will be used to test for differences in protein administration at each time point for the control and experimental groups. The same method will be used to test differences in all secondary outcomes between groups. Additional statistical modelling using generalised linear models will be performed to inspect relationships between baseline patient characteristics, and primary and secondary outcomes.

All analyses on primary and secondary endpoints will be calculated by the study team in close collaboration with the Clinical Trial Unit of the University Hospital Basel.

#### Interim analyses

Interim analyses will be performed by the monitoring team. Data entry into the eCRF will be checked daily for completeness by the study team. The source data/documents will be accessible to monitors, and study-related questions will be answered during possible monitoring visits.

The sponsor-investigator may terminate the study prematurely in the following cases:
Ethical concernsInsufficient participant recruitmentWhen the safety of the participants is in question or at riskAlterations in accepted clinical practice that make the continuation of a clinical trial unwise (e.g. evidence against early enteral nutrition)Early evidence of benefit or harm of the experimental intervention

The trial will be stopped immediately. The participants and/or next of kin will be notified about the termination of the study. All collected associated data of the participants will be used for a preliminary analysis. This includes all associated muscle biopsies, ultrasound images and all values reported in the eCRF.

#### Methods for additional analyses (e.g. subgroup analyses)

We stratified for patients suffering from neurotrauma, which will represent a subgroup for analysis.

#### Methods in analysis to handle protocol non-adherence and any statistical methods to handle missing data

Despite the low number of participants, no considerable amount of missing data is expected due to the close observation of patients on the ICU in addition to our stipulations for replacing withdrawn patients according to the protocol. As described under the “Patient informed consent” section, the patients and their next of kin will have the option to agree to study participation whilst rejecting performance of muscle biopsies. Nevertheless, the study team is interested in obtaining as much study data as possible but will accept missing data on secondary outcomes due to lack of consent for the muscle biopsy. Patients with missing muscle biopsies will not be replaced. No imputation of missing data will be performed for statistical analysis.

#### Plans to give access to the full protocol, participant-level data and statistical code

The sponsor has full access to all data in the study and takes responsibility for the integrity of the data and the accuracy of the data analysis. The datasets analysed during the current study are available from the sponsor or the corresponding author on reasonable request.

### Oversight and monitoring

#### Composition of the coordinating centre and trial steering committee

The trial will be organised and managed by the research team of the intensive care unit in collaboration with the ICU staff. Muscle ultrasonography and biopsies of the quadriceps will be performed by the study team. Assessment of the other secondary outcomes will be supervised by advanced nurse practitioners. Monitoring will be provided by an experienced study nurse. REDCap data collection system will be established by the study team together with the REDCap collaborator at the University Hospital Basel. A member of the study team will conduct daily monitoring of eCRF performance. The statistical research plan and statistical analysis will be supervised by the Clinical Trial Unit, University Hospital Basel.

Co-enrolment of study participants in other clinical trials will be allowed but will have to be discussed among the competing research teams prior to randomisation.

